## Abstract

In the United States (US), new firefighters’ fitness and health behaviors deteriorate rapidly after fire academy graduation. Over the long-term, this increases their risks for chronic diseases. This study protocol describes the proposed usability testing and pilot study of a newly designed and developed healthy lifestyle smartphone app, “Surviving & Thriving”, tailored towards young US firefighters. “Surviving & Thriving” will provide interactive educational content on four lifestyle factors; nutrition, sleep, physical activity, and resilience, and include a personalized journey, habit tracker, and elements of gamification to promote engagement and long-term healthy behavior change. The first phase of the app development entails alpha testing by the research team and pre-beta testing by a fire service expert panel which will help refine the app into a pre-consumer version. Upon completion of the full app prototype, beta ‘usability’ testing will be conducted among new fire academy graduates from two New England fire academies to collect qualitative and quantitative feedback via focus groups and satisfaction surveys, respectively. A last phase of piloting the app will evaluate the app’s efficacy at maintaining/improving healthy lifestyle behaviors, mental health metrics, and physical fitness metrics. We will also evaluate whether firefighters’ perceived “health cultures” scores (ratings of each fire station’s/fire department’s environments as to encouraging/discouraging healthy behaviors) modify the changes in health metrics after utilizing the app for three to six months. This novel user-friendly app seeks to help new firefighters maintain/improve their health and fitness more effectively, reducing their risk of lifestyle-related chronic disease. Firefighters who can establish healthy habits early in their careers are more likely to sustain them throughout their lives.

## Introduction

1

Cardiovascular diseases (CVD) account for 45% of on-duty deaths among United States (US) firefighters (1, 2). Moreover, leading risk factors for heart disease, such as overweight, obesity and metabolic syndrome, are highly prevalent among firefighters (3, 4). Even among younger firefighters, sudden cardiac death has been associated with preventable risk factors, in particular obesity and hypertension (5). Therefore, the career fire service represents a working population at high risk for obesity, CVD, and cancer (1, 6–8) Nonetheless, evidence has suggested public health strategies targeting firefighters’ lifestyle may help reduce risk factors and prevent the onset of chronic disease and premature death (9–12). A healthy lifestyle (HLS) is an evidence-based synergy of behaviors that has been associated with increased well-being and cardiopulmonary fitness, improved anthropometrics and cardiometabolic parameters, and lower blood pressure among firefighters, decreasing disability and chronic disease in this high CVD risk working population (12, 13).

Health promotion programs have demonstrated positive health effects across diverse workplaces, including the fire service (14, 15). As an exemplary HLS, numerous studies have demonstrated that the traditional Mediterranean lifestyle and diet are effective for reducing cancer death, CVD morbidity and mortality, and all-cause mortality (16, 17). Physical activity interventions have also suggested risk reductions for CVD, workplace injuries and occupational stress, as well as improvements in physical fitness and muscular strength (18–20). Yet, firefighters are often quite sedentary in their workplaces (3), and exercise programs are rarely mandated. In addition, due to the nature of shift work, many firefighters report poor sleep quality, sleep disturbances, and sleep disorders, which have been associated with impaired cardiometabolic and mental health outcomes (21–23). Firefighters are also repeatedly exposed to traumatic events which may pose a significant burden on mental health (24). Nevertheless, preventive strategies for resilience training on mindfulness, emotional intelligence, and stress management for first responders have demonstrated positive health benefits (25).

Career firefighter recruits in the US typically undergo formal training in a designated Fire Academy for 12-20 weeks before becoming new or “probationary” firefighters during their first year of service (26). A recent study demonstrated that fire academy training significantly improved recruits’ body composition, aerobic capacity (1.5-mile run), muscular strength (push-up and pull-up), and muscular endurance (10). However, these fitness and health benefits significantly decreased before these recruits finished their probationary period after academy training. Moreover, firefighters after graduating from the fire academy began to exercise less, eat more poorly, and blood pressure continued to increase despite the health/fitness improvements gained during academy training (7, 24, 27). Nonetheless, a recently implemented HLS intervention in firefighters’ academy training showed improvements in healthy lifestyle behaviors, blood pressure, and mental health (11).

The primary aim of this study is to develop and pilot a user-friendly HLS smartphone application (app) tailored towards new probationary firefighters to consolidate and extend academy/training-derived health benefits into firefighters’ first year in the fire service, and then beyond. The first phase of our research project includes the compiling and designing of educational content for a multicomponent lifestyle intervention addressing physical activity, nutrition, sleep, and resilience, the corresponding app software development, and testing of the minimal viable product (MVP). In the second and third phases of this project, we will test the final HLS app prototype’s user-acceptance and effectiveness. The pilot study will evaluate the app’s ability to engage new firefighters and demonstrate whether adherence to the HLS app-based content is associated with measurable health benefits. New firefighters who can maintain a healthy lifestyle during their initial year in the fire service will be more likely to maintain good health behaviors throughout their careers.

We propose the following three aims for the development, usability testing, and piloting of this novel study intervention tool:

Aim 1- HLS app prototype: Develop a smartphone app for future utilization as a digital HLS intervention directed at new US firefighters. Alpha testing by the study team and pre-beta testing by a fire service expert panel will provide feedback on the MVP to enhance the ‘end-user ready’ *Surviving & Thriving* app.

Aim 2- Usability testing: Conduct beta testing of the HLS app prototype by fire academy graduates working as probationary firefighters among veteran firefighters in typical career fire service environments. This field pilot test includes collecting the users’ qualitative and quantitative feedback regarding user acceptance via focus groups and satisfaction surveys, respectively.

Aim 3- Pilot study: Assess the HLS app for its ability to maintain adherence to the HLS app content for at least 3-6 months and its effects on maintaining/improving HLS parameters (HLS scores, physical fitness, and behavioral health (trauma/depression) screeners) in US career firefighters.

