### Pilot study phase

3.3

This phase of the study aims to demonstrate that enrolled participants from the new firefighter study population can maintain adherence to the HLS app for at least 3-6 months. We will recruit ~50 new firefighters (a separate cohort from those enrolled in the beta testing) and monitor their app usage. App metrics such as session duration, screen views, and user retention within the app will provide insights into how users interact with the app over time. This cohort of new firefighters for the pilot study phase will also assess the HLS app’s ability to maintain/improve HLS parameters (HLS scores, physical fitness, mental health (trauma/depression) screeners). For the purposes of this pilot study, we will conduct a small single arm trial which aims to obtain preliminary evidence of the efficacy of a novel digital intervention and to collect qualitative feedback from a subgroup of target users. Changes in HLS parameters throughout the pilot testing will be evaluated with repeated measures of health metrics pre-and-post app usage among those participants that engaged in the HLS app for 3-6 months. Namely, participants will receive the same lifestyle and mental health questionnaires and fitness test at the two time points: before using the HLS app and at the subsequent follow-up (i.e. 3-6 months after). Both adherence and efficacy results will be adjusted for the potential influence of new firefighters’ demographic characteristics. Effect modification analysis will include fire crew, station and department cultures/policies (measured by the “Health Culture” score as mentioned below in 3.3.4.).

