In the pilot study phase, Aim 3, adherence to the HLS app will be measured continuously as the total number of engagements with the software by each participant over the 3 to 6-month pilot study. This outcome will be supported by other prespecified app-usage metrics facilitated by the Managed IT Services provider (i.e. app user information; sign-ins, quest completion rate for each level, frequency of habit tracker use, and number of missions initiated). The primary outcome for validating the efficacy of the HLS app among the new firefighters’ will be the changes in the HLS score, comparing the participants’ pre- and post- app-usage scores (10). Using a behavior change measure (i.e. HLS score) as a primary outcome is justified in an intervention of short duration (11). As secondary outcomes, we will evaluate changes in 1-min pushups and mental health parameters. In addition, we will examine whether the health culture in various fire service workplace environments, as measured by the Health Culture score, influences the intervention effect of the app on the primary and secondary outcomes.

Generalized linear models will be utilized to assess the effect of the proposed app intervention comparing pre and post HLS scores, mental health scores, and 1-min push-up capacity upon completion of 3-6 months of app usage. All models will have their assumptions verified, using analysis of the residuals and other diagnostic testing. Generalized linear modeling will be used to model changes over time after taking into consideration the specific variance-covariance structure of repeated measurements or using other statistical methods such as generalized estimating equations models. All models will be adjusted for demographic and working conditions and other potential confounders. Interaction terms will also be incorporated into the models to evaluate any potential effect modification by working conditions, cultures, and policies. Statistical significance for all analyses will be considered as a two-tailed *p*<0.05.

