We recognize that our study and app prototype have some potential limitations. First, a potential response bias is dependent on quest completion rates and overall evaluations of individual performance and progress, which greatly rely on what the user reports and/or uploads, which may not be congruent with their actual behavior. Second, participants will be aware of their participation in a pilot study of a lifestyle behavior change tool and the fact that they are under observation, our pilot study will probably be susceptible to performance bias and social desirability. Third, it can be argued that the pilot phase, which spans 3 to 6 months, may be too short to gauge whether the app-based intervention will have a significant impact on the health outcomes of professional firefighters, whose careers are usually decades-long. Regarding the technical features of the app itself, at this stage there is no option to integrate data from other mobile apps that estimate a range of cardiometabolic and other health parameters that the user may be already using. Also, we recognize that there is limited personalization since all users will have the same set of tasks that are required to complete the avatar’s journey. Nonetheless, the order of their weekly quests/tasks will be arranged based on their baseline goal setting.

Ultimately, our goal is to develop and test the usability and feasibility of a viable, user-friendly and engaging HLS app that will help new firefighters maintain and improve their training-derived health/fitness levels more effectively, as compared to those before engaging with the HLS app. Firefighters that engage regularly with the app are expected to demonstrate measurable and plausible changes in the HLS parameters covered by the app (nutrition, sleep, physical activity, resilience) in the desired direction. The current research will support the implementation of this app as the primary intervention strategy in a multi-center controlled trial in the US fire service. The proposed future randomized clinical trial would collect laboratory tests to study the potential effect of this digital intervention on chronic disease risk factors in addition to habitual lifestyle behaviors. Ultimately, by sustaining the academy/training-derived health benefits into the probationary firefighter period, we expect firefighters will be more likely to maintain good health habits throughout their careers and thus increase their career longevity.

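### The Introduction says the pilot will show whether adherence is associated with health benefit, but no stated analysis relates the two, and change is evaluated only in participants engaged for 3-6 months

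*Protocol article*

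**What the plan says.** The Introduction states that the pilot will "demonstrate whether adherence to the HLS app-based content is associated with measurable health benefits". The Discussion returns to the idea: "Firefighters that engage regularly with the app are expected to demonstrate measurable and plausible changes" in the lifestyle parameters that the app covers.

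The formal Aim 3, also in the Introduction, is narrower. It reads "Assess the HLS app for its ability to maintain adherence to the HLS app content for at least 3-6 months and its effects on" maintaining or improving healthy-lifestyle (HLS) parameters, so adherence and effect stand side by side.

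Section 3.3 describes the design: "we will conduct a small single arm trial which aims to obtain preliminary evidence of the efficacy of a novel digital intervention". On usage it says "We will recruit ~50 new firefighters (a separate cohort from those enrolled in the beta testing) and monitor their app usage". Change is to be evaluated with "repeated measures of health metrics pre-and-post app usage among those participants that engaged in the HLS app for 3-6 months".

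Section 3.6 defines adherence as each participant's total number of engagements over the 3 to 6 months and calls it an outcome. Change in HLS score is the primary efficacy outcome. The model statement is "Generalized linear models will be utilized to assess the effect of the proposed app intervention comparing pre and post HLS scores", with mental health scores and push-ups treated the same way. Models are adjusted for demographics, working conditions and other confounders. Interaction terms are named for working conditions, cultures and policies.

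Section 3.5 says that usage is monitored if a participant has completed more than three months of use, with 50 expected.

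**The concern.** Whether adherence is associated with benefit is a question about a relationship between two variables, with adherence on the explanatory side and health change as the outcome. The plan measures both and then reports them in parallel. Followed as written, it gives a description of usage and a pre-post difference, and neither shows whether people who used the app more changed more.

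This matters more because the study has no control arm. A pre-post change can reflect time since graduation, repeat testing or awareness of being observed, and the Discussion acknowledges the last of these. A gradient of change across adherence would not settle causation, but it is the internal comparison the Introduction points to.

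The analysis set adds a second problem. Evaluating change only in those who stayed engaged leaves out people who stopped early. If they change less, the reported average describes persistent users and is larger than the average among all who were given the app. A later controlled trial planned on that figure would start from an optimistic value.

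**Working it through.** **Step 1. Compare the promise with the stated analyses.** The protocol gives no effect size, SD, power or retention rate, so there is no figure of its own to reproduce. The first check is textual.

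| Element | Where | Does it link adherence to change? |
|---|---|---|
| Promise of an association | 1 Introduction | Yes |
| Aim 3 | 1 Introduction | No; two parallel parts |
| Set for evaluating change | 3.3 | No; engaged 3-6 months only |
| Adherence and efficacy each adjusted for demographics | 3.3 | No; separate results |
| Paired pre-post tests | 3.6 | No |
| Models for pre versus post | 3.6 | No adherence term |
| Adjustment variables | 3.6 | Adherence not named |
| Interactions | 3.6 | Working conditions, cultures and policies only |

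No stated analysis uses adherence as exposure, covariate, subgroup or interaction for a health outcome.

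**Step 2. Can the pre-post comparison answer the question indirectly?** Inputs: n = 50 (section 3.3) and two-sided 0.05 (section 3.6). Assumed: mean change 0.5 SD, and a correlation between adherence and change of 0 or 0.4. Simulation, 4,000 runs each:

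| True correlation | Pre-post test rejects | Adherence term rejects |
|---|---|---|
| 0 | 93% | 6% |
| 0.4 | 93% | 84% |

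The pre-post test behaves the same in both cases, so it carries no information on the promised question. The adherence term separates them.

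**Step 3. What can about 50 participants detect?** With Fisher's z, the smallest correlation detectable with 80% power is tanh[(1.960 + 0.842)/√(n − 3)].

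- n = 50: tanh(2.802/6.856) = tanh(0.409) = 0.39
- n = 40: 0.43
- n = 35: 0.46
- n = 25: 0.54

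The last three sizes are assumed retention. At n = 50, power is 28%, 56% and 83% for assumed correlations of 0.2, 0.3 and 0.4.

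**Step 4. What could restricting the set do?** As an illustration only, assume the analysed set is the more adherent half and the true correlation is 0.4, with adherence in SD units.

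- Mean change: 0.50 + 0.4 × √(2/π) = 0.50 + 0.4 × 0.798 = 0.82 SD, against 0.50 SD in everyone. The simulation also gives 0.82.
- Correlation: the SD of adherence in the upper half is √(1 − 2/π) = 0.603, so the correlation falls to 0.4 × 0.603/√(0.84 + 0.16 × 0.363) = 0.25.
- Slope: it stays at 0.4. Its standard error rises from √0.84/√50 = 0.13 to √0.84/(0.603 × √25) = 0.30. Power falls from 84% to 23%.

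Under a linear model the restriction raises the mean change and costs precision, but it does not shrink the slope.

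**Step 5. The adherence measure.** Total engagements over a period of 3 to 6 months mixes intensity with length of follow-up. At the same weekly rate, a participant followed for 6 months accumulates 6/3 = 2 times the count of one followed for 3 months. A rate over a common window avoids this.

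**The case against.** **The sentence is not part of a formal aim.** A reader might infer that the plan leaves a stated aim without a result. It does not. The sentence is introductory prose before the three aims, and Aim 3 asks about adherence and about effects, each of which has an outcome and an analysis. This stands, and it makes withdrawing the sentence a legitimate repair.

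**A weaker reading exists.** The sentence could mean only that people who adhere show benefit compared with their own starting values, which the Discussion names as the comparison. That reading is possible, but it treats a change within adherers as an association with adherence, and Step 2 shows that the two are different.

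**A fuller protocol or analysis plan may hold the model.** An exploratory model could be set out there. But section 3.6 names outcomes, models, adjustment variables and effect modifiers, and section 3.3 states the restriction to engaged participants as a rule. That restriction is a choice already made, so it is more than a missing detail.

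**The restriction concerns duration, and adherence is a count.** A reader might infer that the restriction removes all low adherers and pulls the association toward zero. The documents do not support this. Someone can remain engaged for three months with few engagements, section 3.5 expects 50 to pass three months, and a slope is not attenuated by selection on the explanatory variable. The Discussion's remark on high attrition in app-based interventions gives no rate. This objection stands in full, and the top-half case in Step 4 is only an illustration.

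**The association would be confounded.** Healthier or more motivated firefighters may use the app more, and the Discussion leaves controlled evidence to a later trial. This stands, and the result should be labelled accordingly.

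**Conclusion.** The point holds in a limited form. The Introduction says the pilot will show whether adherence is associated with health benefit, no analysis in section 3.6 relates the two, and section 3.3 evaluates change only in participants engaged for 3-6 months. A pre-post change in that subset does not show whether benefit varies with adherence, and it may overstate the average change if less engaged participants change less.

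The question is unanswered by the stated plan, but it is not unanswerable, since adherence is already defined as a continuous measure for each participant. With about 50 participants, only a correlation near 0.39 or larger would be detected with 80% power, so the result would be exploratory.

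The loss caused by the restriction is mainly precision and range of adherence. Its size is unknown because the protocol gives no retention rate. The effect size, correlations and retained fractions used above are assumptions.

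**What to change.** 1. Add one prespecified exploratory model: post HLS score, and each secondary outcome, on adherence rate (engagements or quests completed per week over a common window), adjusted for the baseline value. Report the slope with a 95% confidence interval and call it an observational association.
2. Run this model and the pre-post analysis in all enrolled participants with a follow-up measure, regardless of engagement. Keep the engaged-only analysis as secondary.
3. Reconcile section 3.5, which ties usage monitoring to more than three months of use, with section 3.3, which says the usage of all of about 50 recruits is monitored. Usage data must exist for low users. Table 1 also defines the post measure by 3-6 months of app engagement, so its timing needs wording that covers people who stopped using the app.

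If the authors do not want this analysis, withdraw the Introduction sentence so that the text matches Aim 3.

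The cost is one extra model, plus follow-up questionnaires, remotely supervised push-up tests and gift cards for low users, whom the present wording leaves out of follow-up. Withdrawing the sentence costs nothing, but it leaves the restriction in section 3.3 in place. In that case the report should say that the change applies to engaged participants only.

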## Materials

2

### Study population & screening procedures

2.1

App development, Aim 1, included alpha testing by the research team and pre-beta testing by a fire service expert panel, which helped refine the app into a pre-consumer version. The research team was comprised of health professionals with expertise in lifestyle behaviors (i.e. nutritionists, exercise physiologist, mental health practitioner, and occupational health physician-clinicians) as well as a UX (user experience) and UI (user interface) designer. The Fire Service expert panel included professionals with current or past experience in firefighting and health promotion in the US fire service. For Aims 2 and 3, the target study population of new firefighters will be recruited from the graduated classes of the research team’s partner fire academies in Connecticut and Massachusetts (MA). These firefighting academies have previously committed to participate in the usability testing and pilot study phases. Each academy trains two classes of fire recruits annually, respectively. The academy staff will assist in the recruitment of previous fire academy graduates and provide information about the study without being directly involved in any research activities. Additionally, the academies will hold an online session for further explanation of participants’ involvement and the online informed consent process. Subsequently, the informed consent form will be distributed to eligible academy graduates. Those who provide consent will specify their preferred contact information for future communication with the study team by text or email.

All new firefighters ≥18 years old, English speakers, and who have completed the training at our partners’ training sites (i.e., Connecticut Fire Academy and Massachusetts Firefighting Academy in Stow, MA) will be eligible to participate in the study, either for usability testing or piloting of the final prototype. We anticipate all recruits at these partner academies will be eligible to participate in this research study, requiring no further screening process. For Aim 2, we will recruit recently graduated firefighters from Stow, MA. For Aim 3, we will recruit fire academy graduates from Connecticut’s fire academy. Therefore, participants in the usability testing will differ from the cohort of probationary firefighters in the pilot phase.

